#### Autonomic dysreflexia incidence rate

AD incidence rate is the number of AD events divided by the total person-time (number of study days completed by each participant) to account for the total number of chances for detecting AD for days not measured because of dropout or a disqualifying adverse event.^47^ An AD event will constitute a participant having a SBP increase from baseline of 20 mm Hg not associated with exercise or SBP >150 mm Hg with complaints of headache, diaphoresis, and/or blurred vision and will be diagnosed by our study team clinicians (physicians and physical therapists).

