### Randomization

Before enrolling the first study participant, a research statistician generated the balanced randomization scheme for treatment allocation at both clinical sites using the R Statistical Package.^21^ This method randomly assigns participants to one of three intervention groups (*N* = 20 per group): 1) tAIH + WALK_tSTIM_, 2) tAIH + WALK_tSHAM_, and 3) Placebo + WALK_tSTIM_ in blocks of 6 participants. Using this scheme, the site coordinator will assign each participant to their respective intervention group in the order in which they complete the walking practice sessions. Although the coordinator informs participants about their possible group assignment, they will be blinded to the treatment they receive (i.e., tAIH or Placebo, WALK_tSTIM_, or WALK_tSHAM_). The clinical raters and trainers will also be unaware of each participant's treatment assignment. Based upon reports from participants blinded during our previous tAIH study,^6^ >75% guessed incorrectly or were uncertain of the breathing intervention received, suggesting that our previous blinding and air delivery methods were effective.

We plan a similar integrity analysis for the stimulation sham protocols (no stimulation). Participants guess the interventions received at the end of each treatment session and indicate their guess confidence using a Likert scale.^22,23^ Using a contingency table and Fisher's exact test, we will determine whether the probability of correct guessing differs from chance.

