### Experiment protocol

We developed a study protocol to measure the extent to which tAIH priming boosts the efficacy and potency of training-related functional gains in persons with chronic SCI (Fig. 1). Study participants enroll in 23 intervention and assessment sessions at one of the two clinical trial sites (Fig. 3). Physical therapists serve as trainers and raters; they complete competency and protocol training before their study involvement to ensure rater and training reliability within and between the clinical sites. The interventions consist of eight sessions of walking practice followed by eight combinatorial treatment sessions (four sessions per week for 4 consecutive weeks).

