**FIG. 3. f3:**
[figure not shown]
Timeline of interventions and assessments. After the initial screening visit (S), each intervention consists of eight sessions of walking training (WALK) alone, followed by eight additional sessions of tAIH or Placebo before WALK_tSTIM_ or WALK_tSHAM_. Assessments occur at baseline (BL), at the end of intervention weeks 2 (T_0_), 3 (T_1_), and 4 (T_2_), and, again, after 1 (F_1_), 4 (F_4_), and 8 weeks (F_8_) after the last intervention session. tAIH, therapeutic intermittent hypoxia; WALK_tSTIM_, transcutaneous spinal stimulation-enhanced walking therapy.

We anticipate that tAIH before WALK_tSTIM_ will exceed the benefits of walking practice (WALK), tAIH + WALK_tSHAM_, or Placebo + WALK_tSTIM_ on enhancing the performance of the trained task of overground walking. Justification for the treatment sequence of tAIH followed by WALK_tSTIM_ is based on the estimated time (minutes) required for tAIH to facilitate expression of BDNF.^27^ Applying tAIH ∼1 h before WALK_tSTIM_ may promote temporal alignment of mechanisms of WALK_tSTIM_ neuromodulation with complementary mechanisms of tAIH-induced plasticity that involve BDNF. Details on these interventions are below.

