#### Blood pressure

We will define a systemic hypertensive event as a systolic pressure exceeding 140 mm Hg and/or diastolic pressure exceeding 90 mm Hg.^46^ For each participant, we specifically record the hypertension incident rate, that is, the number of hypertensive events divided by units of person-measures (the total number of BP measurements), which accounts for the total number of chances for detecting a hypertensive event and for measurements not made because of dropout or a disqualifying adverse event.^47^

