Daily tAIH priming enhances the potency of WALK_tSTIM_ on improving walking speed in people with chronic SCI. We quantify potency as the number of tAIH + WALK_tSTIM_ sessions (eight total) needed to achieve the MCID in walking speed.^57^ We assess walking speed with the 10MWT at the end of each training session and predict that those who receive tAIH + WALK_tSTIM_ will achieve an MCID with fewer training sessions than either treatment alone (Placebo + WALK_tSTIM_ or tAIH + WALK_tSHAM_). To test this hypothesis, we will use linear mixed models with number of sessions to achieve the MCID as the outcome with treatment group and 10MWT speed at baseline as fixed effects and participant as the random effect. We anticipate that improvement in walking recovery also will correlate with improved 6MWT, TUG, SCI-FAI, WISCI II, and LEMS scores, suggesting the clinical relevance of this intervention across impairment levels and walking deficits.

#### Hypothesis 3

Daily tAIH+WALK_tSTIM_ does not induce maladaptive changes (spasticity, pain, systemic hypertension, and AD) in persons with chronic SCI. We predict no difference in SCATS, NPRS, CVLT, O-TMT, NBDS, and NBSS scores after daily tAIH + WALK_tSTIM_ compared to baseline. We will use a Friedman two-way repeated-measures ANOVA by ranks to compare these relative scores between and within groups. Changes in these scores relative to baseline are the repeated measures. Intervention (tAIH + WALK_tSTIM_, Placebo + WALK_tSTIM_, and tAIH + WALK_tSHAM_) and time are the fixed main effects, with subject as the random effect. We also predict that tAIH + WALK_tSTIM_ will not elicit a greater incidence of systemic hypertension or AD in persons with chronic SCI.

To test these subhypotheses, we will compare the incidence rates of these maladaptive changes between interventions using the relative risk.^58,59^ A relative risk of 1 will indicate no association between the maladaptive measures and interventions. Using the 95% confidence interval of the relative risk,^59^ we will determine whether there is a statistically significant association between interventions. We predict that the relative risk of hypertension and AD are not different between tAIH versus placebo interventions and WALK_tSTIM_ versus WALK_tSHAM_ interventions.

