### Adverse event reporting

The research team will record adverse events related to each participant from the time of enrollment to the last follow-up assessment visit, which include: 1) unintentional loss of balance (i.e., fall to the ground); 2) change in systolic pressure to >140 mm Hg and/or diastolic pressure exceeding >90 mm Hg^46,60^; 3) AD with SBP >150 or >20 mm Hg from baseline with complaints of headache, diaphoresis, and/or blurred vision; 4) musculoskeletal injury during/after walking training (i.e., sprain, fracture, etc.); 5) symptoms such as pain, soreness, numbness, or signs of injury (inflammation, blisters, etc.) during or immediately after training or on returning home; 6) hospitalization for any cause; and 7) death attributable to any cause. Serious and/or unexpected adverse events will be immediately reported to the MGB IRB.

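### The autonomic dysreflexia and hypertension rates compared between arms include days and readings from before any assigned treatment, which can pull the relative risk towards 1

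*Protocol article*

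**What the plan says.** In the protocol article, Outcome measures defines two safety rates. The section on autonomic dysreflexia gives this definition: "AD incidence rate is the number of AD events divided by the total person-time (number of study days completed by each participant". Under Blood pressure, the hypertension rate is "the number of hypertensive events divided by units of person-measures (the total number of BP measurements". The reason given for both denominators is to allow for measurements or days lost to dropout or a disqualifying adverse event.

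Under Statistical analysis, Hypothesis 3: "we will compare the incidence rates of these maladaptive changes between interventions using the relative risk". The judgement is then made "Using the 95% confidence interval of the relative risk", and the authors predict no difference between arms.

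On timing, Experiment protocol states: "The interventions consist of eight sessions of walking practice followed by eight combinatorial treatment sessions". The legend of Figure 3 agrees: "each intervention consists of eight sessions of walking training (WALK) alone, followed by eight additional sessions of tAIH or Placebo". Under Randomization, participants are put into their groups "in the order in which they complete the walking practice sessions". Adverse events are recorded "from the time of enrollment to the last follow-up assessment visit" (Adverse event reporting). Blood pressure is taken at every walking-practice session (Walking practice) and at baseline, intervention, testing and follow-up visits (Table 2).

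**The concern.** Everyone first completes two weeks of walking practice without hypoxia, placebo, stimulation or sham. Assigned treatment cannot cause an event in those weeks, yet as the rates are written such events count in the numerator and those days or readings count in the denominator of the quantity compared between arms. Allowing for dropout does not require this: days or readings completed after treatment starts would serve equally well.

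The direction matters because Hypothesis 3 is a claim of no harm. Time that treatment cannot influence adds the same expected background to every arm and moves the ratio towards 1. A real excess of AD or hypertension during or after treatment would look smaller than it is, in the direction that supports the prediction.

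**Working it through.** **Session count.** 8 walking-only + 8 combined + 7 assessments (BL, T0, T1, T2 and follow-ups at 1, 4 and 8 weeks) = 23, which reproduces the article's figure of 23 sessions, screening not counted. BL, the 8 walking-only sessions and T0 precede any assigned treatment: 10 of 23 (43%). Treatment sessions are 8 of 23 (35%). T1, T2 and the three follow-ups make the other 5.

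**Formula.** Let *f* be the share of the denominator in which the treatment effect acts, *R* the true relative risk there, and *b* the event rate elsewhere divided by the comparator's rate where the effect acts. *b* is taken as equal in all arms. Then

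observed ratio = [*f·R* + (1 − *f*)·*b*] / [*f* + (1 − *f*)·*b*].

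The documents give no value for *b*. It is an assumption, so a range is shown.

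**AD, session days, R = 3.**

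| *b* | Effect persists from first treatment session (*f* = 13/23) | Effect confined to treatment sessions (*f* = 8/23) |
|---|---|---|
| 1 | (39 + 10)/23 = 2.13 | (24 + 15)/23 = 1.70 |
| 0.5 | (39 + 5)/18 = 2.44 | (24 + 7.5)/15.5 = 2.03 |
| 0.25 | (39 + 2.5)/15.5 = 2.68 | (24 + 3.75)/11.75 = 2.36 |
| 0 | 3.00 | 3.00 |

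**AD, calendar days, R = 3, b = 1.** The article does not say whether a study day is a session day or a calendar day. Taking 2 + 2 + 8 weeks = 84 days, with 14 before treatment: persistent effect (70 × 3 + 14)/84 = 2.67; effect confined to the 14 treatment days (14 × 3 + 70)/84 = 1.33.

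**Hypertension, per reading, R = 3, b = 1.** During the breathing sessions blood pressure is read at every fifth breathing interval (Therapeutic acute intermittent hypoxia). Fifteen episodes give about 3 readings, or about 6 if the room-air intervals also count. With readings around the session and in walking practice, assume 4 to 9 per treatment session and 1 at each of the other 15 visits.
- At 4 per session: 8 × 4 = 32 of 47 readings (68%); (32 × 3 + 15)/47 = 2.36.
- At 9 per session: 8 × 9 = 72 of 87 readings (83%); (72 × 3 + 15)/87 = 2.66.

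Both figures confine the effect to treatment sessions. If it persists, they become (37 × 3 + 10)/47 = 2.57 and (77 × 3 + 10)/87 = 2.77.

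**Starting the window at the first assigned session, R = 3, b = 1.** A persistent effect is recovered in full: 3. An effect confined to treatment sessions reads (8 × 3 + 5)/13 = 2.23 on session days and (14 × 3 + 56)/70 = 1.40 on calendar days. It is recovered in full only when the treatment period is also shown on its own.

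**The case against.** The strongest reply is that attenuation is not automatic. If no events occur outside the treated period, the extra days enlarge every arm's denominator alike and the ratio does not move. Only severe recurrent AD is excluded, but that exclusion, and the provision that a 20 mm Hg rise must not be associated with exercise, could both keep background AD low. This stands: the size is unknown. A zero background is nevertheless hard to assume. Milder AD is not excluded. For hypertension, the stated systolic exclusion is above 150 mm Hg while an event is counted above 140 mm Hg, so a participant between the two could produce events at any visit.

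A reader might infer that both rates rest on total time in the study. The hypertension rate does not: its denominator is readings, which are concentrated in the breathing sessions, so its loss is smaller.

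A reader might also put the whole drop to 1.70 or 1.33 down to the pre-treatment weeks. Those figures also treat T1, T2 and follow-up as unaffected. On calendar days, removing only the pre-treatment weeks moves 1.33 to 1.40, and the rest is follow-up. The trial looks for lasting change, so follow-up is a legitimate period in which to look for harm; including it is a choice of estimand, not an error.

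Nor can one say that a participant withdrawn at the first treatment session would contribute mainly unexposed days. The text at the end of Statistical analysis excludes from analysis anyone who misses more than two sessions.

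Finally, the Gait section describes these measures as capturing changes that follow the combined interventions, and a condensed article may leave exact windows to a fuller document. That shows intent, but here the article does state the denominators, and neither they nor Hypothesis 3 carries that restriction.

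**Conclusion.** The point holds in limited form. As written, both rates include 10 of 23 session days (or the readings taken on them) before any assigned treatment, and nothing in the article limits the window. With background events in that period, the relative risk is attenuated towards the predicted result. For a true relative risk of 3 with equal background, AD on session days reads 2.13 (persistent effect) or 1.70 (effect confined to treatment sessions); hypertension reads about 2.4 to 2.7 on the assumed reading counts. With no background events there is no attenuation. These figures rest on an assumed background rate, equal in all arms, and for hypertension on assumed numbers of readings.

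The documents do not support the stronger conclusion that the safety comparison is certain to miss harm. The pre-treatment schedule is the same in all arms, so the defect is loss of sensitivity of unknown size, not a systematic false signal. Individual adverse events are still recorded, and a research monitor oversees safety.

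**What to change.** In Blood pressure and Autonomic dysreflexia incidence rate, state that for the between-arm comparison, events and days (or readings) count only from the first assigned treatment session onward, with the same window for numerator and denominator. State whether a study day is a session day or a calendar day.

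Report the treatment phase and follow-up separately as well as combined, and say in which of the two T1 and T2 fall. Ending the comparison at T2 is not needed and would set delayed harm aside. Use the BL-to-T0 data only descriptively or as a covariate. Recording of adverse events from enrollment stays as it is.

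The change is to wording only; no new data are needed. The price is fewer events in the comparison and a somewhat wider interval, in exchange for an estimate that no longer contains events that treatment could not have caused.

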#### Cognitive ability

We will assess cognitive function after the last walking practice session and after the last intervention session (T_0_, T_2_; Fig. 3).^48^ The California Verbal Learning Test, Third Edition (CVLT3) brief form will quantify verbal learning and memory.^49^ We also assess executive function with the Oral Trail Making Test (O-TMT).^50^ These tests examine the areas of cognitive ability most likely to be affected by an excessive dose of low oxygen, such as during severe sleep apnea.^51^

#### Bowel and bladder function

We qualitatively assess bowel and bladder function using standardized self-reported questionnaires: the Neurogenic Bowel Dysfunction Score (NBDS) version 2.1 and the Neurogenic Bladder Symptom Score (NBSS).^52–55^ These questionnaires show high test-retest reliability and interpretability.

### Statistical analysis

We plan to test three subhypotheses using parametric and non-parametric statistical inference methods. Statistical significance corresponds to a *p* value <0.05.

#### Hypothesis 1

Daily tAIH + WALK_tSTIM_ enhances overground walking ability in persons with chronic SCI compared to tAIH + WALK_tSHAM_ or Placebo + WALK_tSTIM_.

We predict a decrease in 10MWT and TUG time and an increase in 6MWT distance relative to baseline after tAIH + WALK_tSTIM_ (vs. Placebo + WALK_tSTIM_, tAIH + WALK_tSHAM_). We quantify walking ability using three outcome measures: change in TUG, 10MWT, and 6MWT relative to baseline assessments. Change in performance on these measures will occur after the last intervention session and again at 1-, 4-, and 12-week post-intervention follow-ups (Fig. 3). We will test three related subhypotheses using a linear mixed model with intervention (tAIH + WALK_tSTIM_, tAIH + WALK_tSHAM_, and Placebo + WALK_tSTIM_) and time (visit number) as the fixed main effects, with subject as random effect, whereas scores for TUG (time), 10MWT (time), and 6MWT (distance) will be considered as repeated measures.^56^

Differences from assessment after completion of the walking practice sessions will be compared between and within interventions at tests (T_1_, T_2_) and follow-ups (1, 4, and 8 weeks post-intervention). If analyses of variance (ANOVAs) reveal significant differences, the Tukey-Kramer *post hoc* test will identify pair-wise differences. If walking performance measures at the end of the walking practice sessions are significantly different between intervention groups, we will use an analysis of covariance. We also plan to fit a linear mixed model to test the magnitude and duration of tAIH priming effects based on linear contrasts after controlling for the study period, baseline primary outcomes, and demographics data.

#### Hypothesis 2

Daily tAIH priming enhances the potency of WALK_tSTIM_ on improving walking speed in people with chronic SCI. We quantify potency as the number of tAIH + WALK_tSTIM_ sessions (eight total) needed to achieve the MCID in walking speed.^57^ We assess walking speed with the 10MWT at the end of each training session and predict that those who receive tAIH + WALK_tSTIM_ will achieve an MCID with fewer training sessions than either treatment alone (Placebo + WALK_tSTIM_ or tAIH + WALK_tSHAM_). To test this hypothesis, we will use linear mixed models with number of sessions to achieve the MCID as the outcome with treatment group and 10MWT speed at baseline as fixed effects and participant as the random effect. We anticipate that improvement in walking recovery also will correlate with improved 6MWT, TUG, SCI-FAI, WISCI II, and LEMS scores, suggesting the clinical relevance of this intervention across impairment levels and walking deficits.

#### Hypothesis 3

Daily tAIH+WALK_tSTIM_ does not induce maladaptive changes (spasticity, pain, systemic hypertension, and AD) in persons with chronic SCI. We predict no difference in SCATS, NPRS, CVLT, O-TMT, NBDS, and NBSS scores after daily tAIH + WALK_tSTIM_ compared to baseline. We will use a Friedman two-way repeated-measures ANOVA by ranks to compare these relative scores between and within groups. Changes in these scores relative to baseline are the repeated measures. Intervention (tAIH + WALK_tSTIM_, Placebo + WALK_tSTIM_, and tAIH + WALK_tSHAM_) and time are the fixed main effects, with subject as the random effect. We also predict that tAIH + WALK_tSTIM_ will not elicit a greater incidence of systemic hypertension or AD in persons with chronic SCI.

To test these subhypotheses, we will compare the incidence rates of these maladaptive changes between interventions using the relative risk.^58,59^ A relative risk of 1 will indicate no association between the maladaptive measures and interventions. Using the 95% confidence interval of the relative risk,^59^ we will determine whether there is a statistically significant association between interventions. We predict that the relative risk of hypertension and AD are not different between tAIH versus placebo interventions and WALK_tSTIM_ versus WALK_tSHAM_ interventions.

To minimize biases and errors in data collection, a designated lead physical therapist, blinded to study interventions, ensures participant adherence to the protocol and consistent scoring among therapists by regularly checking all assessment logs for adherence to standard clinical procedures. Non-blinded research staff members (including post-doctoral fellows, lab engineers, and research assistants) assist clinicians with training setup and clinical data collection. The study principal investigator oversees all study procedures and ensures the correct collection and documentation of data. If participants miss more than two walking practice sessions or intervention sessions, we will not conduct further assessments and exclude their data from analyses. However, if participants miss an assessment session, we record their data as “missing” at that time point.

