**FIG. 2. f2:**
[figure not shown]
Flow diagram of anticipated subject recruitment, enrollment, intervention allocation, and disposition status. We anticipate *N* = 48 people with SCI to complete the study. SCI, spinal cord injury; tAIH, therapeutic intermittent hypoxia; WALK_tSTIM_, transcutaneous spinal stimulation-enhanced walking therapy.

For Aim 1, our sample-size estimate focused on results from an earlier placebo-controlled clinical trial that reported that persons with incomplete SCI completed the 10-Meter Walk Test (10MWT) faster after tAIH + WALK (−4.3 ± 1.0 sec, faster relative to baseline) as compared to Placebo + WALK (0.9 ± 0.4 sec, slower relative to baseline).^6^ From these results, we conservatively estimated the standard deviation of the 10MWT time relative to baseline as 2.0 sec in Placebo + WALK_tSTIM_ and tAIH + WALK_tSHAM_ and 3.0 sec in tAIH + WALK_tSTIM_. The estimated difference between the change in tAIH + WALK_tSTIM_ and the change in Placebo + WALK_tSTIM_ was −5.2 sec, and that difference between tAIH + WALK_tSTIM_ versus tAIH + WALK_tSHAM_ was estimated as −3.14 sec. Assuming a 20% dropout rate with 16 completers per group, three outcome measures (10MWT, Timed Up and Go Test [TUG], and the 6-Minute Walk Test [6MWT]), and a significance level of 0.0167 adjusted for the three repeated outcomes,^20^ this study will have >99% statistical power in comparing tAIH + WALK_tSTIM_ versus Placebo + WALK_tSTIM_ and >81% statistical power in comparing tAIH + WALK_tSTIM_ versus tAIH + WALK_tSHAM_.

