#### Gait

Overground walking ability is quantified by three primary measures: 10MWT (walking speed); TUG test (walking initiation and balance); and a 6MWT (walking endurance). These tests capture functional ambulation, exhibit high reliability and construct validity, and have precedence for quantifying and distinguishing degrees of functional ambulatory recovery post-SCI.^37–39^ Our previous study in persons with chronic SCI showed these tests to be more sensitive to changes in walking function and functional ambulation compared to American Spinal Injury Association Impairment Scale (AIS) grade or categorical ambulation metrics.^6,8^ During all walking assessments, we allow participants to use their least restrictive hand-held assistive device of choice.

Participants carry out two trials each for the 10MWT and TUG (at their fastest but comfortable and safe speed); the average speed will be used. A minimum of a 1-min rest between tests will be provided. Participants will perform the 6MWT only once at a walking speed sustainable for 6 min. The participant's walking distance at the 2- and 6-min mark will be recorded. We also record secondary outcome measures of walking function that include the Walking Index for Spinal Cord Injury (WISCI) II^40^ and SCI Functional Ambulation Index (SCI-FAI).^41^ To quantify strength, the AIS lower extremity motor scores (LEMSs) will be used.^42^

To quantify maladaptive changes that may occur subsequent to the combinatorial interventions, we measure pain, spasticity, systemic hypertension, AD, and cognitive ability during our assessments.

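### Aim 1 is powered at 0.0167 per primary outcome, but the analysis section judges the same three outcomes at p<0.05 and does not say which test is primary

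*Protocol article*

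**What the plan says.** All references are to the protocol article.

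- **Sample size (Aim 1).** Power is computed at "a significance level of 0.0167 adjusted for the three repeated outcomes", with 16 completers per group. The SDs of the 10MWT change are "2.0 sec in Placebo + WALK_tSTIM_ and tAIH + WALK_tSHAM_ and 3.0 sec in tAIH + WALK_tSTIM". The assumed differences are −5.2 s against Placebo + WALK_tSTIM and −3.14 s against tAIH + WALK_tSHAM. The stated power is >99% and >81% respectively.
- **Gait.** "Overground walking ability is quantified by three primary measures: 10MWT (walking speed"; TUG and 6MWT are the other two.
- **Statistical analysis, opening.** "Statistical significance corresponds to a *p* value <0.05". The figure 0.0167 does not reappear, and no adjustment across outcomes is mentioned.
- **Statistical analysis, Hypothesis 1.** A linear mixed model takes intervention "and time (visit number) as the fixed main effects, with subject as random effect". Differences are "compared between and within interventions at tests (T_1_, T_2_) and follow-ups (1, 4, and 8 weeks post-intervention". After a significant ANOVA, "the Tukey-Kramer *post hoc* test will identify pair-wise differences". No visit or contrast is named as the deciding one.

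**The concern.** Two thresholds are given for the same three primary outcomes, and nothing joins them. The sample size section shows that the sponsor meant to share 5% among the outcomes, but the decision rule in the analysis section does not do so. A result with p between 0.0167 and 0.05 on one outcome, say p = 0.03 on TUG, would be a success under one section and a failure under the other.

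Five visits enter the comparison as well. Tukey-Kramer adjusts for the pairs of arms only, so it covers neither the outcomes nor the visits. If the threshold and the deciding test are settled after the data are seen, the choice can follow the results. The primary efficacy claim depends on it.

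**Working it through.** **1. The sample-size threshold.** 0.05 / 3 = 0.0167, as stated: a Bonferroni split over three outcomes.

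**2. Which threshold the stated power belongs to.** Inputs from the Sample size section: n = 16 per arm, SDs 3.0 s and 2.0 s, differences 3.14 s and 5.2 s.

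- Standard error = √(3²/16 + 2²/16) = √0.8125 = 0.901 s.
- Welch degrees of freedom = 0.8125² / [(9/16)²/15 + (4/16)²/15] = 26.1.
- Noncentrality = 3.14 / 0.901 = 3.48, and 5.2 / 0.901 = 5.77.
- Two-sided critical t = 2.56 at 0.0167 and 2.06 at 0.05.

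| Threshold (two-sided) | Power, 3.14 s | Power, 5.2 s |
|---|---|---|
| 0.0167 | 81.5% | 99.9% |
| 0.05 | 91.8% | >99.9% |

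The plan's >81% and >99% are reproduced at 0.0167. The 3.14 s comparison is the one that discriminates: one-sided 0.0167 would give about 89%, and two-sided 0.05 about 92%. The published power therefore belongs to the 0.0167 rule.

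**3. Family-wise error if the tests were independent.** The formula is 1 − (1 − α)^k.

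- 3 tests: 1 − 0.95³ = 14.3% at 0.05; 1 − 0.9833³ = 4.9% at 0.0167.
- 15 tests (3 outcomes × 5 visits): 1 − 0.95¹⁵ = 53.7% at 0.05; 1 − 0.9833¹⁵ = 22.3% at 0.0167.

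**4. Family-wise error with correlation.** The documents give no correlation between outcomes or visits, so 0.5 to 0.9 is an assumption. The simulation used normal data, three arms of 16, no effect, exchangeable correlations, and a three-arm F test per outcome or per outcome and visit.

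| Correlation (outcomes / visits) | One test per outcome, 0.05 | One test per outcome, 0.0167 | Any of 15, 0.05 | Any of 15, 0.0167 |
|---|---|---|---|---|
| 0.5 / 0.5 | 13% | 5% | 41–43% | 18% |
| 0.5 / 0.7 | 13% | 5% | 35–36% | 15% |
| 0.7 / 0.7 | 11% | 4% | 32% | 13% |
| 0.8 / 0.8 | 10–11% | 4% | 25% | 11% |
| 0.9 / 0.9 | 9% | 3% | 17–18% | 7% |

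With one test per outcome, the figures are the same whether that test uses a single visit or the average over visits.

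**5. A narrower count.** Counting only Tukey-confirmed differences that involve the combination arm, the five-visit figures at 0.05 are about 31%, 26%, 23%, 18% and 13%, in the same row order.

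**The case against.** The 0.05 may be meant as the overall level for a section that covers all three hypotheses, with 0.0167 per outcome understood from the sample size. That is plausible, but the analysis section does not say it, and it offers p<0.05 as the definition of significance. An unseen SAP may well set the order of visits, so the missing visit hierarchy would not be a finding by itself. Two conflicting thresholds in the same article are a different matter.

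A reader might infer that the plan carries a false-positive risk of 17–43%. The documents do not support that as the single answer. The mixed model with an intervention main effect can be read as one group test per outcome, which gives 9–14%. The sentence listing T1, T2 and the follow-ups supports the five-visit reading. Both are open.

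The figures also count any group difference, including one between the two single-modality arms. Hypothesis 1 predicts a benefit of the combination. False Tukey differences at 0.05 that favour it over at least one comparator occur in about 3–5% at one visit and 7–17% over five. This lowers the absolute size, but 5% is then the wrong yardstick: with no effect each arm is equally likely to look best, so a single outcome would give about 0.05/3 = 1.7%.

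A reader might also infer that Tukey-Kramer is wrong here or that the power statement fails. Neither follows. Tukey-Kramer over three pairs is valid, if somewhat conservative for two planned contrasts. Using two-sample tests to size a mixed-model trial is ordinary practice, and the stated figures reproduce.

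**Conclusion.** The point stands as a contradiction within the article: 0.0167 in the sample size and 0.05 in the decision rule, for the same three primary outcomes, with no deciding test named. The stated 10MWT power belongs to two-sided 0.0167.

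Under the global null and the rule as written, the chance of at least one significant primary group difference is about 9–13% with one group test per outcome (14% if independent). It is about 17–43% if any of the five visits can count. Both ranges depend on assumed correlations of 0.5–0.9, and the article does not settle which reading applies. Every case examined exceeds 5%. The 0.0167 rule holds 5% only with one test per outcome.

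**What to change.** In the Statistical analysis section, under Hypothesis 1:

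1. State that 10MWT, TUG and 6MWT are each tested at two-sided 0.0167, or by Holm at an overall 0.05, matching the Sample size section.
2. Name one primary test per outcome: either one visit or one overall intervention contrast. The choice is the sponsor's. Aim 1 concerns enduring effects, so the end of intervention is not the automatic candidate.
3. Label the remaining visit comparisons secondary. Without steps 2 and 3, the 0.0167 threshold still leaves about 7–18% over five visits.

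Tukey-Kramer may stay for the pairs of arms.

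The cost is a stricter threshold per outcome than p<0.05; no participants are added. The stated 10MWT power is unchanged for a direct comparison of changes as assumed in the Sample size section. If the sponsor chose to run Tukey-Kramer itself at 0.0167, power for the 3.14 s difference would be about 78%; the plan does not state that combination. The article gives no effect sizes for TUG or 6MWT, so nothing can be said about their power. The wording should be settled before unblinding.
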